### Statsol nQuery Advisor 5.0: Two group t-test of equal means (equal n's)

|                                                  | 1     | 2     | 3     | 4     | 5     | 6     | 7     | 8     |
|--------------------------------------------------|-------|-------|-------|-------|-------|-------|-------|-------|
| Test significance level, $\alpha$                | 0,050 | 0,050 | 0,050 | 0,050 | 0,050 | 0,050 | 0,050 | 0,050 |
| 1 or 2 sided test?                               | 1     | 2     | 1     | 2     | 1     | 2     | 1     | 2     |
| Group 1 mean, $\mu_1$                            | 4,500 | 4,500 | 4,500 | 4,500 | 4,500 | 4,500 | 4,500 | 4,500 |
| Group 2 mean, $\mu_2$                            | 3,500 | 3,500 | 3,500 | 3,500 | 4,000 | 4,000 | 4,000 | 4,000 |
| Difference in means, $\mu_1 - \mu_2$             | 1,000 | 1,000 | 1,000 | 1,000 | 0,500 | 0,500 | 0,500 | 0,500 |
| Common standard deviation, $\sigma$              | 3,000 | 3,000 | 3,500 | 3,500 | 1,500 | 1,500 | 2,000 | 1,500 |
| Effect size, $\delta =  \mu_1 - \mu_2  / \sigma$ | 0,333 | 0,333 | 0,286 | 0,286 | 0,333 | 0,333 | 0,250 | 0,333 |
| Power ( % )                                      | 98    | 96    | 93    | 89    | 98    | 96    | 87    | 96    |
| n per group                                      | 250   | 250   | 250   | 250   | 250   | 250   | 250   | 250   |

The assumption of at least 4.5 infection episodes is based on a study investigating the frequency, nature and severity of infections throughout the first 3 years of life in relation to three types of child care arrangement (home care, group care (2-6 children), and day care (> 6 children)). In this study it could be observed that the infection rates ranged from 4.5 episodes in the first year of life for infants with home care to more than 7 episodes for infants in day care centers (Wald ER et al. 1991. J Pediatr 118:509-514). Among the different illnesses, upper respiratory tract infection (URTI) was most prominent with 3.8 episodes for infants with home care up to 6.3 episodes for infants in day care centers in the first year of life.

The assumption of a standard deviation of maximum 3.5 episodes is based on the same publication in which the above described results were observed with standard deviations between 2 (home care) and 3 episodes (group care).

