## 6. STUDY PARAMETERS

### 6.1 Primary outcome parameter

The primary outcome parameter is the number of febrile episodes (peak rectal temperature at least 38.5 °C) during the first year of life.

The febrile episode is considered as finished if the child is again without fever and other symptoms. Another febrile episode is considered as new period if the fever occurs at least three days after the stated time of recovery from a previous episode.

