## 10.5 Number of subjects and study power

Starting with 500 formula infants per group, it is assumed that about 35% will be lost for the per-protocol-analysis due to continuation of breastfeeding beyond the second month of life and further about 15% due to different dropout / withdrawal reasons so that 250 infants per formula group fully completing the study should be achieved.

With those 250 formula infants per group completing the study without violation of the protocol, a reduction of the mean number of febrile episodes by 1 which is considered as clinically relevant reduction (from 4.5 to 3.5, SD 3.5 episodes), compared to placebo can be proven with 93% power in an one-sided unpaired t-test or 89% in a two-sided unpaired t-test.

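### Section 10.5 states 93%/89% power for febrile episodes with a mean and SD taken from infection episodes, so the power is not supported for the primary endpoint and may be overstated

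*Protocol*

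**What the plan says.** Protocol section 6.1 defines the endpoint: "The primary outcome parameter is the number of febrile episodes (peak rectal temperature at least 38.5 °C) during the first year of life". Sections 5 and 13.1 use the same definition. Symptoms of infection without a fever requirement, such as cough and runny nose, are secondary parameters (sections 5 and 6.2).

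Section 10.5 bases power on the "mean number of febrile episodes by 1 which is considered as clinically relevant reduction (from 4.5 to 3.5, SD 3.5 episodes"), with 250 protocol-compliant completers per group, and states 93% (one-sided) or 89% (two-sided) for an unpaired t-test. The text under the nQuery table explains the inputs: "The assumption of at least 4.5 infection episodes is based on a study investigating the frequency, nature and severity of infections". It adds that "the infection rates ranged from 4.5 episodes in the first year of life for infants with home care", rising to more than 7 in day care, and that "upper respiratory tract infection (URTI) was most prominent with 3.8 episodes for infants with home care". The SD of at most 3.5 is referred to the same publication, which is reported to show "standard deviations between 2 (home care) and 3 episodes (group care").

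All eight table columns use a control mean of 4.5. The last four SD entries, for a difference of 0.5, read "1,500 | 1,500 | 2,000 | 1,500".

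**The concern.** The planning figures are called infection episodes where they are justified and febrile episodes where they are used. The protocol itself treats these as different things, one as the primary endpoint and the other as secondary parameters. In home care 3.8 of the 4.5 source episodes (84%) are upper respiratory infections. The protocol does not say how many of them reach 38.5 °C.

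If febrile episodes are appreciably rarer than 4.5 per infant, one of two things follows. A 1-episode reduction becomes a much larger proportional effect than the 22% implied by 4.5 to 3.5. Or, if the proportional effect is what matters, the absolute difference shrinks and power may fall. In either case section 10.5 does not tell the reader of a null result what effect the trial could have detected on its own endpoint.

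**Working it through.** **Inputs from section 10.5.** Control mean 4.5, active mean 3.5, difference 1.0, SD 3.5, n = 250 per group, alpha 0.05. Source SDs are 2 (home care) and 3 (group care). The completer number follows from 500 × (1 − 0.35 − 0.15) = 250.

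**Step 1: reproduce the stated power.** For a two-group t-test the non-centrality is d / (SD × √(2/n)) with 2n − 2 = 498 degrees of freedom. With d = 1 and SD 3.5 it is 1 / (3.5 × √(2/250)) = 3.19. Power is 93.9% one-sided and 89.0% two-sided, against 93% and 89% stated. The arithmetic is right for its inputs.

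**Step 2: vary the control mean with a relative target.** The protocol gives no febrile rate, so means of 1, 1.5, 2 and 3 are assumed. Also assumed is the same proportional effect, 1 − 3.5/4.5 = 22.2%, so d = 0.222m. Three variance assumptions are shown:

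- A: variance = m + k·m², with k back-calculated from SD 3.5: (3.5² − 4.5)/4.5² = 7.75/20.25 = 0.383. The control-arm variance is used in both arms, as the plan does.
- B: as A, but averaging the two arms' variances.
- C: a constant variance/mean ratio from the home-care SD: 2²/4.5 = 0.889, so variance = 0.889m.

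| Control mean | d | SD (A) | Power A | Power B | SD (C) | Power C |
|---|---|---|---|---|---|---|
| 1.0 | 0.222 | 1.18 | 56% | 62% | 0.94 | 75% |
| 1.5 | 0.333 | 1.54 | 68% | 74% | 1.15 | 90% |
| 2.0 | 0.444 | 1.88 | 75% | 82% | 1.33 | 96% |
| 3.0 | 0.667 | 2.54 | 83% | 89% | 1.63 | 99.5% |

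All figures are two-sided at 5% with 250 per group. At m = 4.5, A returns the plan's 89%. If instead the SD fell in exact proportion to the mean, power would stay at 89% for any mean.

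**Step 3: keep the absolute target of 1 episode.** With the variance in A, two-sided power is above 99% at means of 1.5, 2 and 3. The target is then 1/3 = 33%, 1/2 = 50% and 1/1.5 = 67% of the control mean, and at a mean of 1 it would remove every episode.

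**Step 4: the table.** Columns 1/2, 3/4 and 5/6 are one-/two-sided pairs at one SD. Column 7 is one-sided at SD 2.0 (87%). Column 8 is two-sided but repeats column 6 (SD 1.5, effect size 0.333, 96%). A two-sided partner to column 7 would have effect size 0.5/2.0 = 0.250 and power 79.7%.

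**The case against.** A reader might infer that the trial does not have the power it states. The documents do not support that. They give neither a rate nor an SD for febrile episodes, a rarer count usually has a smaller SD, and 3.5 is described as a maximum above the source values of 2 to 3. The home-care SD of 2, which belongs to the mean of 4.5, gives a variance of 4, below the mean, so there is no over-dispersion. On that basis power is at or above the stated 89% from a control mean of about 1.5 upward.

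Nor does it strictly follow that the febrile mean is below 4.5. That figure is the home-care end of a range reaching more than 7, and infants in day care are not excluded. As an illustration, 6 infections of which 75% are febrile also average 4.5.

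The 22% relative effect and the 0.383 dispersion are constructions for this check. Section 10.5 names only an absolute reduction of 1. The calculation also concerns per-protocol completers. The intention-to-treat set is larger: with 500 × 0.85 = 425 per group, assumption A gives about 79/88/93/97% at the four means, before any dilution by mixed feeding.

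These objections stand against a claim of proven power loss. They do not supply the missing link between infection and febrile episodes. They show that the answer depends on a figure the protocol does not give.

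Column 8 is consistent within itself, and the headline power rests on columns 3 and 4, so the duplication does not touch the stated 93%/89%.

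**Conclusion.** The stated 93%/89% is correct arithmetic on inputs that describe infection episodes, and the protocol offers no step from those to episodes of at least 38.5 °C. The power is therefore unsupported for the primary endpoint and may be overstated. How far cannot be fixed from the document. For a 22% relative reduction and control means of 1 to 3, it runs from 56–83% (dispersion from SD 3.5, control-arm variance) to 75–99.5% (ratio from SD 2). If the 1-episode target is meant literally, the weak point is whether the effect is plausible, not power: it would be a third to two thirds of all febrile episodes at means of 3 to 1.5.

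The duplicated column 8 is a minor side correction.

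**What to change.** In section 10.5:

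- State the assumed control rate and SD of febrile episodes (at least 38.5 °C), or an assumed febrile fraction of the infection rate, with its basis.
- Say whether the target is an absolute reduction of 1 or a relative reduction, and why it is relevant at that rate.
- Restate power for 250 per group over a range of control means, for example 1 to 3, with the variance assumption named.
- In the table, check column 8. If it was meant to pair with column 7, it should read SD 2.0, effect size 0.250 and 80% two-sided power. Flag the SD 1.5 columns as lying below the cited range of 2 to 3.

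The cost is a rewrite of one section and one table. The endpoint, conduct and enrolment do not change. The restated power may be less favourable and should be reported as it comes out.

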## 10.6 Compensation to study subjects

Mothers randomised into a formula feeding group will receive the respective study formula free of charge throughout the study, i.e. until their infants are 1 year of age.

Mothers participating in the reference group with full breastfeeding for at least 4 months will receive a Numico local follow-on formula for the second half of the first year free of charge –if needed and requested.

At the end of the study and after the planned blood drawings in the subgroups, the respective infants (including breastfed infants in the reference group) will receive a small present (e.g. a cuddle toy).

Parents will not get any financial compensation for their participation in the study.

## **11. STUDY TEST PRODUCTS**

### **11.1 Basic product composition and packaging / blinding**

Group 1 (Active Formula Group): Non-hydrolysed cow's milk based formula containing an immunomodulating mixture of

- Neutral oligosaccharides: galacto-oligosaccharides and fructo-oligosaccharides (inulin) in a ratio of 9:1 and a dosage of 0.68 gram per 100 ml
- Acidic oligosaccharides: pectin hydrolysate, dosage of 0.12 gram per 100 ml

Group 2 (Control / Placebo Group): Standard non-hydrolysed cow's milk based formula with the same composition as the active formula but without supplementation.

To avoid any immunological effect by other ingredients, both formulas will not contain other supplementations with suspected immunological influence such as probiotics, LCPUFA, or nucleotides. The only difference between the two formulas is the presence or absence of the supplemented mixture of neutral and acidic oligosaccharides.

Formulas will be supplied as powder in 400 g tins. The infants will receive starting formula (IF) until the age of 6 months and follow-on formula (FOF) thereafter. The composition of the products is given in the appendix.

The labels on the tins will be multi-language labels (English, Dutch, German, Italian) to cover all languages used in this multi-centric study. Examples are given in the annex. As the labels are anonymous neither the clinicians / nurses / mothers who give the feedings to the infants nor the persons performing the examinations and the statistical evaluations of the data will know about the identity of the formulas.

The allocation of the two blinded formula tin variants, only differing in a small hidden detail, to the individual infants will be performed by persons not involved in the study (hospital pharmacy). According to the randomisation list provided by NUMICO, the formula tins will be allocated to the respective subject and labelled with the respective randomisation number on the lid (numbered labels provided by NUMICO). For unblinding of study subjects –if necessary\*- a sealed envelope is provided by NUMICO with a letter (example see annex) containing the allocation code (information how by means of the hidden detail the formula can be identified).

\*The unblinding of a study subject should be left to the case that an unexpected serious adverse event occurs which requires the knowledge about the feeding regimen as basis for any decision on the therapy.

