## **9. STUDY GROUPS**

There will be two formula groups in the study:

- Group 1: Active Formula Group on full formula feeding after 2 months at the latest receiving a non-hydrolysed cow's milk based formula containing an immunomodulating mixture of neutral and acidic oligosaccharides. To avoid any immunological influence by other ingredients, the formula will not contain any other special supplementation such as probiotics, LCPUFA, or nucleotides.
- Group 2: Control Group on full formula feeding after 2 months at the latest receiving as placebo a standard non-hydrolysed cow's milk based formula with the same composition as the active formula but without supplementation of oligosaccharides. Other ingredients with suspected immunological influence will also not be supplemented, i.e. the only difference between the two formulas is the presence or absence of the supplemented mixture of neutral and acidic oligosaccharides.

The allocation to the two formula groups will be performed in a randomised way according to the stratified randomisation table (see annex) at study entry.

As non-randomised reference group, infants on full breastfeeding for at least 4 months will serve.

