## 21. APPENDIX

### 21.1 Composition of study formulas

The final details of the composition of the follow-on formulas are not yet definitive.

| Nutrients
per 100 ml        | Unit            | Experimental
starting
formula

13.6 g
powder | Control
starting
formula

13.1 g
powder | Experimental
follow-on
formula

14.5 g
powder | Control
follow-on
formula

14.5 g
powder |
|--------------------------------|-----------------|-------------------------------------------------------------|--------------------------------------------------------|--------------------------------------------------------------|---------------------------------------------------------|
| Energy                         | kJ              | 275                                                         | 280                                                    | 280                                                          | 293                                                     |
| Energy                         | kcal            | 65                                                          | 67                                                     | 67                                                           | 70                                                      |
| Protein                        | g               | 1.3                                                         | 1.4                                                    | 1.4                                                          | 1.8                                                     |
| Fat                            | g               | 3.4                                                         | 3.5                                                    | 3.2                                                          | 3.4                                                     |
| Linoleic acid                  | mg              | 520                                                         | 397                                                    | 489                                                          | 489                                                     |
| $\alpha$ -Linolenic acid       | mg              | 96                                                          | 73                                                     | 91                                                           | 91                                                      |

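### The formulas are said to differ only in the oligosaccharide mixture, but the composition table shows many other differences, so an effect cannot be attributed to the mixture

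*Protocol*

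**What the plan says.** Section 9 describes the control as a standard formula "with the same composition as the active formula but without supplementation of oligosaccharides" and adds that "the only difference between the two formulas is the presence or absence of the supplemented mixture" of oligosaccharides. The synopsis (Test groups) also says the compositions are the same. Section 11.1 repeats the claim: "The only difference between the two formulas is the presence or absence of the supplemented mixture of neutral and acidic oligosaccharides". It then directs the reader to the table: "The composition of the products is given in the appendix".

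Appendix 21.1 lists the nutrients per 100 ml in four columns: active starting, control starting, active follow-on and control follow-on. Two rows show the pattern: "Linoleic acid | mg | 520 | 397 | 489 | 489" and "Protein | g | 1.3 | 1.4 | 1.4 | 1.8". The table carries one caveat, which concerns the follow-on products only: "The final details of the composition of the follow-on formulas are not yet definitive".

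Sections 4 and 5 frame the aim and hypothesis as the effect of supplementing formula with the oligosaccharide mixture.

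**The concern.** Sections 9 and 11.1 make the control the active formula minus the supplement. If that were true, any randomised difference could be credited to the supplement. If the base recipes also differ, the trial compares two complete products, and the mixture is one of several differences between them.

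The protocol's own rationale makes this more than a formality. Section 3 counts lipids, including polyunsaturated fatty acids, and proteins among the components of breast milk that support gut and immune maturation. Sections 9 and 11.1 keep LCPUFA, probiotics and nucleotides out of both formulas so that nothing else could act on the immune system. Yet two polyunsaturated fatty acids differ between the starting formulas, and protein differs between the follow-on formulas.

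The ambiguity runs in every direction. A reduction in febrile episodes might come from the base recipe, and a null result might hide an effect offset by it. Growth and tolerance are safety outcomes (sections 6.3 and 13.6) for which section 14.3 assumes equivalence, but energy and protein also differ by arm.

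**Working it through.** **Inputs.** All values come from the Appendix 21.1 table, per 100 ml. It has 42 rows. Three of them are the supplement itself (fibres, GOS/FOS, acidic oligosaccharides), leaving 39. Energy appears in both kJ and kcal; counted once, that leaves 38.

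**Row count, active versus control.**
- Starting formula: 20 of 38 rows differ.
- Follow-on formula: 14 of 38 rows differ.
- At least one of the two stages: 26 of 38 rows differ.

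**Size.** Relative difference = active / control − 1. For starting-formula selenium, 2.5/1.5 − 1 = +67%; for follow-on iron, 0.71/1.26 − 1 = −44%.

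| Nutrient | Starting: active vs control | Difference | Follow-on: active vs control | Difference |
|---|---|---|---|---|
| Selenium (mcg) | 2.5 vs 1.5 | +67% | 2.5 vs 1.5 | +67% |
| Linoleic acid (mg) | 520 vs 397 | +31% | 489 vs 489 | 0 |
| Alpha-linolenic acid (mg) | 96 vs 73 | +32% | 91 vs 91 | 0 |
| Potassium (mg) | 77 vs 64 | +20% | 78 vs 78 | 0 |
| L-carnitine (mg) | 1.0 vs none | – | none vs none | 0 |
| Vitamin A (mcg RE) | 51 vs 60 | −15% | 55 vs 55 | 0 |
| Protein (g) | 1.3 vs 1.4 | −7% | 1.4 vs 1.8 | −22% |
| Energy (kcal) | 65 vs 67 | −3% | 67 vs 70 | −4% |
| Iron (mg) | 0.5 vs 0.5 | 0 | 0.71 vs 1.26 | −44% |
| Zinc (mg) | 0.5 vs 0.5 | 0 | 0.6 vs 0.9 | −33% |
| Vitamin D3 (mcg) | 1.4 vs 1.4 | 0 | 1.4 vs 1.9 | −26% |
| Calcium (mg) | 52 vs 52 | 0 | 78 vs 88 | −11% |

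**Could the supplement's own bulk explain this?** The mixture weighs 0.68 + 0.12 = 0.8 g. Assume it displaces the rest of the powder in proportion.
- Follow-on: both formulas use 14.5 g of powder, so other nutrients would fall by 0.8/14.5 = 5.5%. Iron, zinc, vitamin D3 and protein fall by 22 to 44%.
- Starting: the powder weights are 13.6 and 13.1 g. The non-supplement part is (13.6 − 0.8)/13.1 = 12.8/13.1 = 0.977 of the control, a fall of about 2%.
- Displacement cannot raise a nutrient, so it explains none of the selenium, fatty acid, potassium or L-carnitine differences.

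**Is the fat itself different?** Linoleic acid per gram of fat in the starting formulas is 520/3.4 = 153 mg (active) and 397/3.5 = 113 mg (control). The fat blends differ.

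**Does lower energy density explain the protein gap?** Follow-on protein per 100 kcal is 1.4/67 × 100 = 2.1 g against 1.8/70 × 100 = 2.6 g. It does not.

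**Are these typing errors?** Energy at 4, 9 and 4 kcal per g of protein, fat and carbohydrate:
- Active starting: 5.2 + 30.6 + 29.2 = 65.0 (table 65)
- Control starting: 5.6 + 31.5 + 30.0 = 67.1 (table 67)
- Active follow-on: 5.6 + 28.8 + 32.8 = 67.2 (table 67)
- Control follow-on: 7.2 + 30.6 + 32.4 = 70.2 (table 70)

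The macronutrient differences are therefore internally consistent. This check says nothing about the micronutrients.

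**Could the analysis repair it?** Sections 10.4 and 14.1 plan adjustment for characteristics of infant, family and feeding. Composition is the same for every infant within an arm, so its effect cannot be estimated apart from the arm effect, by any model or at any sample size.

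**The case against.** Several points on the other side are fair.

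- **The consequence is not demonstrated.** Nothing in the protocol shows that these amounts of selenium, iron, zinc or vitamin D3 change the number of febrile episodes. That stands: the direction and size of any distortion are unknown. But the protocol rests attribution on identical base recipes, and once that premise fails it offers nothing in its place.
- **The iron, zinc, vitamin D3 and protein figures are provisional.** They are follow-on values, marked as not final, and the first three do not differ in the starting formula. Follow-on feeding begins at 6 months, after weaning foods are allowed (section 11.5), so formula is only part of intake by then. That also stands. The starting formula has no such caveat, is fed until 6 months, and establishes the contradiction alone.
- **The row count overstates the matter.** Of the 20 differing starting-formula rows, 10 are within 10%, and fat and protein differ by one unit in the last printed digit. True, but the other 10 include selenium, both fatty acids, potassium and L-carnitine.
- **The specific exclusions hold.** The table lists no probiotics, LCPUFA or nucleotides in either arm. Agreed; it is the broader sole-difference claim that fails.
- **The hypothesis already compares formula with formula.** Section 5 does name the placebo formula as comparator. It still describes the intervention as supplementation with the mixture, and sections 9 and 11.1 define that as the sole contrast.
- **Randomisation, type I error and power are untouched.** Correct, for the comparison of whole formulas.

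**Conclusion.** The protocol contradicts itself on what the intervention is. By its own table the starting formulas differ in 20 of 38 non-supplement rows, with gaps up to +67% (selenium) and one ingredient, L-carnitine, found only in the active product. The follow-on formulas differ in 14 of 38, with gaps from −44% (iron) to +67% (selenium), on figures that may have changed later.

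The randomised comparison of the complete formulas remains valid. What is lost is attribution of an effect, or of its absence, to the oligosaccharide mixture, and that is the question in sections 4 and 5. The verdict assumes that the starting-formula columns describe the product actually fed. It does not assume that any particular nutrient difference affects febrile episodes. A statistical analysis plan cannot cure this, because the problem lies in the product specification.

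**What to change.** 1. Reconcile the synopsis, section 9 and section 11.1 with Appendix 21.1, and state the composition of the products actually fed.
2. While the follow-on recipe is still open, fix one common base for both arms that differs only in the oligosaccharides. The sponsor's nutrition and clinical experts should choose the levels. Do the same for the starting formulas where still possible.
3. Where a common base is not possible, delete the sole-difference and same-composition statements, list the remaining differences, and word the objective, hypothesis and conclusions as the complete active formula versus the complete control formula, for efficacy and safety alike.

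**Cost.** Steps 1 and 3 are text changes in the synopsis, sections 9 and 11.1, and the aim and hypothesis. Randomisation, sample size and analysis are unaffected. Step 2 should be cheapest before the follow-on recipe is frozen, but the protocol gives no manufacturing information and both label versions in section 21.2 are already headed as final, so its real cost is for the sponsor to establish.
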